## Abstract

**Background:**

Following lumbar fusion surgery, a successful outcome is empirically linked to effective rehabilitation. While rehabilitation is typically postoperative, the phase before surgery – termed *prehabilitation* – is reportedly an ideal time to prepare the patient. There are presently no guidelines for prehabilitation before lumbar fusion surgery. Physical activity has well-known health benefits, and staying physically active despite pain is a major principle in non-pharmacological chronic low back pain treatment. Psychological factors such as fear of movement, pain catastrophizing and low self-efficacy are known to be barriers to staying active. No studies have investigated prehabilitation protocols that promote physical activity and target psychological risk factors before lumbar fusion surgery. The aim of our proposed randomised controlled trial is to investigate whether patients who undergo lumbar fusion surgery for degenerative disc disease experience better functioning with a physiotherapeutic prehabilitation program (PREPARE) based on a cognitive behavioural approach compared to conventional care.

**Methods/Design:**

We will recruit 110 patients between 18–70 years of age with degenerative disc disease who are waiting for lumbar fusion surgery. These patients will be randomly assigned to receive either PREPARE or conventional care. PREPARE uses a person-centred perspective and focuses on promoting physical activity and targeting psychological risk factors before surgery. The primary outcome will be disability measured using the Oswestry Disability Index 2.0. Secondary outcomes will include functioning (patient-reported and performance-based), physical activity (accelerometer), health-related quality of life, back and leg pain intensity, pain catastrophizing, kinesiophobia, self-efficacy, depression, anxiety, satisfaction with treatment results and health economic factors. Data will be collected at baseline (preoperatively) after the intervention (preoperatively), 3 and 8 weeks, 3, 6, 12, 24 and 60 months postoperatively.

**Discussion:**

We hypothesise that the focus on promoting physical activity and targeting psychological risk factors before surgery will decrease disability and help the patients to be more active despite pain both before and after surgery. We will use a combination of outcome measures both patient-reported and performance-based, as well as accelerometer data. This will provide a more comprehensive picture of the patient’s functioning than just patient-reported outcomes alone.

**Trial registration:**

Current Controlled Trials ISCRTN17115599, Retrospectively Registered 18 May 2015.

## Background

Lumbar degenerative disc disease (DDD) is a subgroup of chronic low back pain (CLBP). When pain and disability are severe, lumbar fusion surgery can be an option [1]. The frequency of lumbar spinal fusion surgery is increasing worldwide [2, 3]. In 2008, DDD was the most common diagnosis prior to spinal fusion surgery in the USA [4]. In 2013, the Swedish Spine Register recorded 8144 patients with degenerative lumbar spine disorders, of which approximately 10 % had a primary diagnosis of DDD or isthmic spondylolisthesis and underwent lumbar fusion surgery [5]. The DDD group is an interesting study group for several reasons. They are relatively young [5], and their lack of functioning has hence a large impact on their life and on society. Clinical experience dictates that most patients choose fusion surgery to enable them to continue to work and to live an active life.

While rehabilitation traditionally starts postoperatively, the phase before surgery – termed *prehabilitation* – is suggested to be an ideal time to prepare patients for an optimal outcome of surgery [6, 7]. A small number of studies of low-quality suggest that there is no evidence for the effectiveness of physiotherapy interventions before and after lumbar fusion, and hence best practice remains unclear [8]. We lack guidelines for the pre and post-operative phase for this patient group [9, 10], but there are national and international guidelines for conservative or non-pharmacological treatment for patients with CLBP. These guidelines incorporate major treatment principles, such as to stay active despite pain along with supervised exercise therapy, cognitive behavioural therapy and multidisciplinary treatment [11]. There is no reason to believe that patients with DDD would not benefit from the same treatment principles.

The benefits of staying or becoming more physically active are manifold. The major underlying rationale is the effect of physical activity on general health [12, 13]. On a global level physical inactivity is one of the global burdens, leading to premature death and non-communicable diseases [13]. It is hence important to promote physical activity in all conditions, patients with CLBP alike. Patients with DDD who choose to undergo surgery have experienced pain for several years, and 52 % of them reported that they are able to walk less than one kilometre [3]. However, there are presently little data regarding physical activity levels in this patient group. In addition to its general health benefits, physical activity has an analgesic effect that likely involves several partially overlapping mechanisms [14, 15]. The hypoalgesic effect of exercise on pain is usually reduced in patients with “more general” chronic pain conditions [14]. However, the exercise-induced hypoalgesic effects in patients with CLBP are reportedly similar to those in healthy individuals [16, 17]. It would hence be of value to promote physical activity for patients with DDD.

There are various reasons for not being physically active. One factor is the perception and attitude towards exercises [18]. Another factor is fear of movement. This factor has been identified as an important mediator in combination with catastrophizing thoughts regarding disability, disuse and depression in patients with CLBP [19]. It appeared that 70 % of the patients with CLBP who visited an orthopaedic department in Sweden for a potential fusion surgery reported kinesiophobia [20]. Even though the prevalence of kinesiophobia among patients with DDD is unknown, research suggests that the prevalence of kinesiophobia in patients with specific CLBP is similar to that in patients with non-specific CLBP [21]. Furthermore, pre-surgical psychological status such as pain catastrophizing [22], negative outcome expectations [23] and fear-avoidance beliefs [24] have been found to be significant predictors of pain and function up to 2 years after lumbar surgery. Hence, we hypothesise that the majority of persons who are waiting to undergo surgery for DDD suffers from a high degree of pain, kinesiophobia, catastrophizing and low self-efficacy – and all of these factors may contribute to a low physical activity level. Hence, an intervention using a cognitive behavioural approach could be appropriate to target these risk factors. Given the multidimensional nature of pain, rehabilitation programs based on cognitive-behavioural therapies (CBT) have been specifically recommended for patients with CLBP and are often used in addition to other therapies such as exercise [25].

Although the importance of post-lumbar surgery rehabilitation programs targeting the above-mentioned psychological factors have been emphasised [26–28], so far only two programs have yielded successful outcomes following lumbar fusion surgery [28, 29]. Abbott et al. compared postoperative psychomotor therapy with exercise therapy in a randomised controlled trial (RCT) that included 107 patients undergoing lumbar fusion surgery for spinal stenosis, spondylosis, degenerative/isthmic spondylolisthesis or DDD. The psychomotor therapy program combined motor control exercises for lumbopelvic stabilisation with a cognitive behavioural intervention immediately after surgery. This treatment was more effective compared to exercise therapy in reducing disability and fear-avoidance beliefs and in increasing self-efficacy and outcome expectancy at 2 and 3 years post-surgery [28]. Another recent RCT compared a rehabilitation program including active exercise alone with a treatment combining active exercise with the management of catastrophizing and fear of movement among 130 patients undergoing lumbar fusion surgery for degenerative spondylolisthesis and/or lumbar spinal stenosis. The combined rehabilitation program showed superior disability reduction measured by the Oswestry Disability Index (ODI) at the 1-year follow-up [29].

These prior investigations have been performed after lumbar fusion surgery. However, some authors hypothesise that further optimisation of lumbar fusion surgery outcomes may be possible by initiating an intervention *before* surgery [26, 30]. Nielsen et al. found their intervention to be superior to conventional care with regards to postoperative functionality assessed by the Roland-Morris Disability Questionnaire, faster recovery and shorter hospital stay. The content of the intervention was an individualised preoperative training program that focused on improvement of muscular back strength as well as cardiovascular conditioning before spinal fusion surgery [26].

To our knowledge, at the start of our trial (2014), no prior study had assessed the use of a prehabilitation program with individual sessions to target psychological risk factors – such as fear-avoidance beliefs and low self-efficacy – to maintain or increase physical activity both before and after surgery. Therefore, we initiated an RCT to evaluate a physiotherapeutic prehabilitation program called PREPARE (*Pre*habilitation, *P*hysical *A*ctivity and exe*R*cis*E*).

### Aim of the study

The overall aim of the trial is to investigate whether PREPARE – a physiotherapeutic prehabilitation program based on a cognitive behavioural approach – will improve functioning after lumbar fusion surgery in patients with DDD compared to conventional care.

### Hypotheses

Patients who receive PREPARE – a physiotherapeutic person-centred prehabilitation program based on a cognitive behavioural approach – before spinal fusion surgery will experience decreased disability levels, improved functioning, increased physical activity level, better health-related quality of life, decreased leg and back pain intensity, less pain catastrophizing, less pain-related fear, increased self-efficacy to exercise and less depressed mood after surgery compared to patients who receive conventional care. We further hypothesise that the between-groups difference will be largest at 6 months after surgery.Compared to those in the control group, patients who receive PREPARE will show a more rapid increase in their physical activity level measured objectively with an accelerometer at 3 and 6 months after surgery.From a societal perspective, PREPARE will be more cost-effective and show higher cost-utilities compared to conventional care at one year after surgery.

## Methods/Design

### Trial design

A prospective RCT will be performed at a private spine clinic in Gothenburg, Sweden. Participants will be randomised to one of the two arms of the trial.

### Theoretical Framework

The PREPARE program combines different philosophical standpoints, theoretical models and treatment principles.

Pain is defined as *“an unpleasant and emotional experience associated with actual or potential tissue damage, or described in terms of such damage”* [31], and is hence to be considered a subjective phenomenon. As PREPARE rests on the assumption that pain is subjective, we will apply the principles of person-centred care (PCC). In PCC, emphasis is placed on recognising the patient as a human being with reason, will, feelings, and need, and on engaging the patient as an active partner in his/her care and treatment [32]. The most important parts in PCC is the partnership between the patient and the therapist and to formulate a health plan together with the patient which includes both short-and long-term goals along with the actions needed to reach each goal.

Modern pain research has led to a shift in treatment strategies, from pain reduction to pain management with a focus on teaching patients to manage their thoughts (cognitive component) and feelings (affective component), which are both pain-related components. PREPARE will target fear-avoidance beliefs, as well as self-efficacy, which are regarded as important for a person’s ability to stay active despite pain [33]. For patients of working age with LBP, evidence suggests that treatment should include cognitive behavioural techniques combined with physical activity [34]. Self-efficacy is a concept that explains a person’s confidence in their ability to perform a specific activity [35]. In patients with LBP, both self-efficacy and fear-avoidance beliefs are possible predictors of disability [33, 36]. However, since it remains unclear how these two constructs differ in predicting disability, it is suggested that therapists measure and consider both constructs when treating patients with LBP [36, 37]. To achieve this, the physiotherapist will use a combination of techniques based on a cognitive behavioural approach [38]. Figure 1 presents an overview of the fear-avoidance model including the mediating role of self-efficacy.

**Fig. 1 Fig1:**
[figure not shown]
The fear-avoidance model with the mediating role of self-efficacy

### Participants

We will recruit a total of 110 patients of 18–70 years of age, who have major complaints of DDD: CLBP of motion-elicited type degenerative changes of 1-3 segments of the lumbar spine, reproducible pain in clinical examination assessed to originate in the same segment as demonstrating degenerative changes, and on the waiting list for lumbar fusion surgery. Patients may have additional minor radiating symptoms with or without simultaneous surgical procedure for disc herniation, foraminal decompression, or isthmic spondylolisthesis. The trial will exclude patients who have undergone previous decompression surgery for spinal stenosis or who have spinal malignancy, dominating radiculopathy, a confirmed neurological disorder or rheumatic disorder, deformities in the thoracolumbar spine (e.g. idiopathic scoliosis), or a poor understanding of the Swedish language.

### Recruitment and randomization

Trial participants will be recruited from two private spine clinics and one university hospital. Patients will be clinically examined by an orthopaedic surgeon, who will make a medical diagnosis based on the clinical and radiological findings. Patients who are diagnosed with DDD will be informed that lumbar fusion surgery is a treatment option. When a patient agrees to undergo surgery and is placed on the waiting list, the hospital and the spine clinics coordinators will inform the physiotherapist (*PT-prepare*) who will deliver the trial intervention. Then the *PT-prepare* will call the patient to inform him/her of the trial and invite him/her to participate.

Patients interested in participating will meet with an independent observer at baseline, 8–12 weeks before surgery at one of the private spine clinics. The independent observer will once again provide the patient with information about the trial. If the patient agrees to participate, he/she will sign an informed consent form provided by the independent observer. The independent observer will then guide the participant through the functional capacity testing and provide him/her with the patient-reported outcome measures and the accelerometer. After this, the independent observer will give the participant a sealed envelope containing the group allocation.

The participant will be randomly allocated to Group A or Group B using a computerised random list with no restrictions, arranged by an independent statistician. The project leader – who will not take part in the intervention and outcome assessments – will be responsible for arranging sequentially numbered, opaque, sealed envelopes. To conceal the group allocation, the participant will not open this envelope in the presence of the independent observer. The allocation list will be stored in a locked fire-proof cupboard at the university laboratory, in accordance with the principles of the ethical approval.

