### Blinding

The independent observer who is responsible for all measurements will be blinded to the treatment allocation. The trial participants will be aware of the treatment that they receive, but will not know the content of the treatment in the control group. The *PT-Prepare* will not be blinded since she is delivering the treatment for Group A.

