#### Secondary outcome measures (effect evaluation)

Patient-reported functioning will be measured using the Swedish version of the Patient-Specific Functional Scale (PSFS). In the PSFS, the patient lists three activities that are limited by the condition for which he/she is seeking treatment. The patient then rates their perceived difficulty in performing each of the listed activities on a scale from 0 to 10, with 0 indicating that the patient cannot perform the activity at all. The three separate scores are averaged to generate the total score The English version of the PSFS is responsive to clinically important change over time [45], and shows good test–retest reliability and strong criterion validity [46] for patients with CLBP.Performance-based functioning will be measured using five tests: 5-min walking (measurement of the distance the patient can walk in 5 min); 50-feet fast walking (measurement of the time it takes for a patient to walk 50 feet as fast as possible); the Timed up-and-go (measurement of the time it takes for a patient to arise from a chair, walk three meters, turn around, walk back to the chair and sit down); 1-min stair-climbing (measurement of the number of steps the patient can climb in one minute) [47, 48]; and the One-Leg Stand Test (measurement of the duration the patient can stand on one leg, with eyes open and with eyes closed) [49]. Findings support the construct validity of these tests and show that they have adequate test–retest reliability for patients with CLBP [47–49].A digital triaxial accelerometer (ActiGraph GT3X+; ActiGraph, Pensacola, FL, USA) will be used to assess physical activity as steps per day, time spent at different intensity levels and time spent sedentary [50, 51]. The GT3X+ measures acceleration in three planes and the raw output is “counts”. Based on the number of counts per minute, the raw output is classified into time spent at different intensities of physical activity and time spent sedentary by using appropriate cut-points in the complementary software, Actilife 6 (ActiGraph, Pensacola, FL, USA). The device will be attached with an elastic band to the patient’s right iliac crests during waking hours for a 7-day period. The patient will be instructed to remove the device while sleeping, swimming and bathing. The GT3X+ has shown high construct validity when measuring physical activity intensity levels [50] and excellent criterion validity when measuring the number of steps [51] in healthy adults.Health-related quality of life will be measured using the Swedish version of the European Quality of Life 5 Dimensions Questionnaire (EQ-5D). In the EQ-5D, patients rate their health on five items relating to mobility, self-care, usual activities, pain/discomfort and anxiety/depression. The patient also rates his/her general health on a visual analogue scale. The English version of the EQ-5D has acceptable test–retest reliability and findings support its construct validity for patients with chronic musculoskeletal pain [52].Health-related quality of life will also be measured using the Swedish version of the Short Form (36) Health Survey (SF-36). The SF-36 comprises eight scaled sections: vitality, physical functioning, bodily pain, general health perceptions, physical role functioning, emotional role functioning, social role functioning and mental health [53]. The Swedish version of the SF-36 shows high internal consistency and high discriminant validity and findings support its construct validity in a Swedish population sample [54].Back and leg pain intensity levels over the last week will be measured using 100-mm Visual Analogue Scales (VAS) [55]. Findings support the validity and reliability of the VAS in patients with chronic pain [56].Pain will also be measured using a 5-point scale with the following response options: pain-free, much better, better, unchanged, or worse. This scale shows good responsiveness for patients with CLBP undergoing lumbar fusion surgery [57].Pain catastrophizing will be measured using the Swedish version of the Pain Catastrophizing Scale (PCS), which includes 13 items assessing catastrophizing thoughts about pain. The PCS has shown adequate internal consistency and high construct validity in a Swedish population sample [58].Kinesiophobia will be subjectively rated using the Swedish version of the Tampa Scale of Kinesiophobia (TSK-SV). The TSK comprises 17 items assessing the subjective kinesiophobia rating. The TSK-SV has shown high test–retest reliability and internal consistency, and has support for its face, content and construct validity in patients with CLBP [59].Self-efficacy related to exercise will be measured using the Swedish version of the Self-Efficacy for Exercise scale (SEE-SV). On the SEE-SV, the patient rates his/her confidence that he/she could exercise three times per week (20 min each session) under nine different conditions – for example, “if you experienced pain while you exercised” or “if you felt tired”. The SEE-SV shows substantial test–retest reliability and satisfactory internal consistency and content validity for older adults [60].Anxiety and depression will be assessed using the Swedish version of the Hospital Anxiety and Depression Scale (HADS) [61]. In a Swedish population sample, the HADS showed moderate internal consistency and high construct validity [62].Satisfaction with treatment results will be measured using a 3-point scale with the following response options: satisfied, uncertain, or dissatisfied.PHODA is an instrument that is conventionally used to determine the perceived harmfulness of daily activities in patients with LBP [39]. In this trial, we will use a modified version of PHODA to capture the patients’ beliefs and attitudes regarding activity behaviour, rather than the expected harmfulness. The original PHODA is extended with photos of leisure-based activities that the patient is also asked to rate in the above-described manner. The modified PHODA will not be used to measure outcomes of the present trial, but will rather be employed as a tool to supply the *PT-prepare* with information about the patient’s activity behaviour in relation to the pictured physical activities and the motives underlying the activity behaviour.

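### The allocation envelope is handed over before the 7-day baseline accelerometer week, so allocation can be known while baseline activity is recorded

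*Protocol article*

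**What the plan says.** The protocol article (Recruitment and randomization) describes a single baseline meeting: "Patients interested in participating will meet with an independent observer at baseline, 8–12 weeks before surgery at one of the private spine clinics". After consent, the observer takes the participant through the functional capacity tests and will "provide him/her with the patient-reported outcome measures and the accelerometer". The next step is: "After this, the independent observer will give the participant a sealed envelope containing the group allocation". On when it may be opened, the article says only that "the participant will not open this envelope in the presence of the independent observer".

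Under Secondary outcome measures (effect evaluation), the accelerometer is worn at the hip "during waking hours for a 7-day period". Under Blinding: "The trial participants will be aware of the treatment that they receive".

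Under Hypotheses, patients given PREPARE "will show a more rapid increase in their physical activity level measured objectively with an accelerometer at 3 and 6 months after surgery". Under Effect evaluation, activity level is compared between groups at 3 and 6 months with a two-sample t-test. The same section plans a linear mixed model with random intercept for the repeated measures, and an exploration of mediation and interaction.

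**The concern.** A baseline value should be fixed before the participant can learn the allocation. The functional tests meet this condition, because they are finished before the envelope changes hands. The accelerometer record does not, because it only begins to accumulate once the device has been handed out.

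The rule about opening the envelope protects the observer's blinding. It does nothing to protect the baseline. A participant who learns that he or she has been assigned to a programme promoting physical activity may behave differently in the monitored week from one who learns of assignment to conventional care. If so, baseline activity would differ between the groups because of allocation, and an analysis that treats it as a pre-treatment value would misstate the change. The hypothesis of a faster rise in activity is worded in terms of such a change.

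**Working it through.** **Order of events.**

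1. Day 0: consent, functional tests, then questionnaires and accelerometer supplied (Recruitment and randomization).
2. Day 0, immediately afterwards: envelope handed over (same section).
3. From day 0: 7 days of wear (Secondary outcome measures), with the envelope in the participant's possession.

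A 7-day recording cannot be complete at the visit where the device is supplied. Reading the envelope step as following the completed wear week would require a second contact, and none is described. No instruction to keep the envelope sealed during the wear week is given. It follows that allocation *can* be known during baseline recording. When it is in fact known is not stated.

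**Which planned analyses use the value.**

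| Analysis | Uses baseline activity? |
|---|---|
| ODI at 6 months, two-sample test | No |
| Activity level at 3 and 6 months, two-sample t-test | No |
| Faster rise in activity, as hypothesised | Yes, if tested as worded |
| Linear mixed model, mediation and interaction | Not stated; exposed if baseline activity enters |

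**Size.** The plan has no figure of its own on this point. The only plan figure used is 55 per group, which reproduces from the ODI assumptions: 2 × (1.960 + 0.842)² × (15/8)² ≈ 55.2 per group (two-sided test assumed). It does not bear on the order of events.

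Let X be baseline activity and Y postoperative activity, in SD units with equal SDs, and let δ be the amount by which knowledge of allocation raises Group A's baseline relative to Group B's.

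- *Level comparison at 3 or 6 months:* mean Y in A minus mean Y in B. X does not appear, so the bias is 0.
- *Change-score contrast:* (Y − X) in A minus (Y − X) in B. The bias is −δ, that is, one-for-one.
- *Baseline-adjusted contrast with slope β:* the bias is −βδ.

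The standard error of the change-score contrast, with correlation ρ between X and Y, is √[(2/55) × 2(1 − ρ)]:

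- ρ = 0.5: 0.191
- ρ = 0.6: 0.171
- ρ = 0.7: 0.148

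The documents give neither δ nor ρ. Taking δ = 0.1 to 0.3 SD as an assumed range, the change-score bias runs from 0.1/0.191 ≈ 0.5 to 0.3/0.148 ≈ 2.0 standard errors. Under adjustment with β = ρ (0.5 to 0.7), the bias would be 0.5 × 0.1 = 0.05 to 0.7 × 0.3 = 0.21 SD.

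**The case against.** The strongest reply is that the one test named for the activity comparison uses postoperative levels only. A shifted baseline week leaves it untouched, and the primary outcome likewise. This stands, and it sets the limit of the point. A reader might infer that the planned activity test, or the trial's main result, is biased; the documents do not support that. It is still true that a comparison of levels does not itself describe an increase, so reporting the hypothesis as worded would bring in the exposed baseline.

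Second, the article does not say when the envelope is opened, and the figure showing the baseline and follow-up sessions is not available. A reader might infer that allocation *is* known throughout the wear week. The text supports only that it *can* be. This is nevertheless more than missing operational detail: the article sets out the sequence, and following it as written leaves the baseline unprotected.

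Third, the size and even the sign of a shift are uncertain. The control group is also advised to stay active, and everyone knows that a monitor is being worn. This stands. If Group A alone became more active in that week, a change-score contrast would understate a benefit rather than create one.

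Two further readings are tempting but not established. One is that PREPARE sessions have already begun during the wear week; the article gives only a typical start of about 8 to 12 weeks before surgery. The other is that baseline questionnaires are completed after allocation is learned; they are supplied before the envelope, and when they are filled in is left open.

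**Conclusion.** The point holds in a limited form and is minor. As written, the procedure allows allocation to be known during the baseline activity week, so baseline physical activity cannot be assumed to be a pre-allocation measurement. The primary ODI comparison, its sample size, the functional tests at baseline and the t-tests of activity level at 3 and 6 months are unaffected.

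The exposure is confined to describing the hypothesised rise in activity and to any change-from-baseline, mixed-model or mediation analysis that uses baseline activity. In a change-score contrast the bias equals the differential baseline shift. That shift is unknown. The range of about 0.5 to 2 standard errors rests on assumed shifts of 0.1 to 0.3 SD, assumed correlations of 0.5 to 0.7 and complete data on 55 per group; it illustrates leverage and is not an estimate of harm.

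**What to change.** For participants still to be enrolled (the Trial status section plans recruitment until December 2016), require the envelope to stay sealed, or release it only, once the 7-day wear and the baseline questionnaires are complete. Set a fixed latest release date, so that failure to return the device does not leave a consented patient unallocated. If participants are already told to wait, one sentence saying so settles the matter.

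For those already enrolled, treat baseline accelerometer data as potentially post-allocation and base conclusions about activity on the postoperative between-group comparison already planned. Opening dates recalled in retrospect would be weak evidence, and the solution should not depend on them.

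The cost is about one week of the 8–12 week preoperative window, plus a mailing or a further contact per participant if the envelope is withheld rather than kept sealed. Keeping it sealed is cheaper but relies on the participant's compliance.
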